Cachexia and malnutrition not only represent symptoms of the disease but also are important factors having a significant impact on the outcome of PDAC patients (9). A low value of fecal elastase-1, depicting impaired exocrine pancreatic function and contributing to cachexia, has been reported to strongly correlate with poor survival in advanced PDAC patients (10). However, cachexia and impaired nutritional status might also affect the tolerance and response to medical treatments such as chemotherapy. This is particularly important in PDAC; not more than 20% of patients are eligible for the resection at the time of the diagnosis (3), while the rest might have an indication for chemotherapy. In this setting, while Gemcitabine mono-chemotherapy has for a long time been the standard treatment for unresectable PDAC with relatively poor effect represented by a median overall survival (OS) around 6 months (11), intensified regimens, such as the combination of 5-fluorouracil, leucovorin, irinotecan, and oxaliplatin (FOLFIRINOX), or the addition of Nab-Paclitaxel to gemcitabine, are nowadays more frequently used, with substantially improved survival (12–17). However, due to their side effects, particularly encountered in FOLFIRINOX, intensified regimens can be less tolerable, leading to dose reduction or therapy discontinuation (13–15), which makes their use limited to the patients with ECOG status of 0, 1, and 2 (15, 16). For patients with ECOG of 3 or higher, the large majority of experts recommend best supportive care (18).

Considering this, it is even more important to assess the impact of the nutritional status in patients with advanced PDAC in order to identify sub-groups at a higher risk of side effects and treatment discontinuation. If timely identified, these patients could be approached and treated accordingly, in order to increase their capacity to complete the planned therapy and therefore possibly improve its efficacy. Studies so far conducted to address this important issue have been too few and limited in terms of parameters evaluated as well as outcomes observed and often did not use standardized measures. Hence, evidence is sparse and heterogeneous.

We, therefore, designed a multicenter prospective study in order to assess the impact of patient's nutritional status on the clinical course of advanced PDAC patients receiving chemotherapy.

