## Methods

### Study Design

The PAncreatic Cancer MAlnutrition and exocrine pancreatic INsufficiency in the course of chemotherapy in unresectable pancreatic cancer (PAC-MAIN) study is a non-profit, international, multicenter, prospective, observational, cohort study evaluating the effect of the nutritional status and pancreatic exocrine function on the main outcomes of patients with advanced PDAC. The study will be carried out in Russia, Turkey, Serbia, Romania, Italy, and Spain as a part of the Pancreas 2000 Educational Program. Pancreas 2000 is a post-graduate educational program that prepares young gastroenterologists, surgeons, radiologists, and other physicians for specialization in Pancreatology (19).

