#### Description of the Intervention (Schedule of Visits)

Visit 1 (screening, within 1 month from initial diagnosis)

Patients will be informed about the study. Once patients agree with the inclusion in the study, we will evaluate the inclusion and exclusion criteria. Those patients who meet all the inclusion criteria and none of the exclusion criteria will be finally included in the study. In this visit, patient-related, tumor-related, and pancreatic function and treatment-related variables will be recorded, and quality of life questionnaire will be administered. The researcher will record weight, height, BMI, and unplanned WL % for the last 6 months.

Each patient's baseline nutrition status will be evaluated using the MNA score prior to starting chemotherapy. Patients will be classified as in the group with no nutritional risk, at risk of malnutrition, or malnourished.

Nutritional parameters and pancreatic function will be evaluated through blood tests and a fecal test.

Visit 2 (3 months after the first dose of planned chemotherapy)

The researcher will record in the CRF the planned chemotherapy, schedule, doses, dose reduction, and any adverse event^1^. The same variables recorded at Visit 1 will be checked again.

Check-up 3 (end of the study, 6 months)

The researcher will record in the CRF the OS and time until progression.

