Multivariable logistic regression analysis will be used to estimate the independent effect of malnutrition status on percent chemotherapy received (<80% chemotherapy received vs. 80% chemotherapy received; binary end point), after controlling for demographic and clinical characteristics (age, sex, race, ECOG status, tumor site, tumor stage, PEI, and DM). The demographic and clinical variables included in the final model will be chosen using a forward-stepwise method. Similarly, multivariable linear regression analysis will be used to estimate the independent effect of nutritional status on mean percent chemotherapy received (i.e., continuous endpoint), after controlling for demographic and clinical characteristics. All *p* values are two-sided with statistical significance evaluated at the 0.05 alpha level. Ninety-five percent confidence intervals (CIs) will be calculated to assess the precision of the obtained estimates (for odds ratios/beta estimates). The Kaplan–Meier method will be used to estimate OS and progression-free survival (PFS). The log-rank test will be used to compare OS and PFS between well-nourished patients and malnourished patients. Greenwood's formula will be used to calculate 95% CIs for Kaplan–Meier survival estimates. The frequency and percentage of missing values for each variable will be collected, analyzed, and reported (missing value analysis). All data will be anonymous once data collection is completed, respecting the confidentiality of the subjects participating, in accordance with data protection laws. All analyses will be performed in STATA 14 (Statacorp LLC, Texas).

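### The only survival comparison named is an unadjusted log-rank test in an observational cohort, and a 6-month end of study makes OS largely overlap with 6-month survival

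*Protocol article*

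**What the plan says.** All references are to the protocol article.

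- **Design (Study Design).** The study is a "prospective, observational, cohort study evaluating the effect of the nutritional status and pancreatic exocrine function" on patient outcomes. The Patients section admits locally advanced and metastatic disease and excludes ECOG 3 or higher, so ECOG 0 to 2 are pooled.
- **Survival analysis (Statistical Analysis).** OS and PFS are estimated by Kaplan-Meier with Greenwood confidence intervals. The group comparison is: "The log-rank test will be used to compare OS and PFS between well-nourished patients and malnourished patients".
- **Adjustment (Statistical Analysis).** It is stated for chemotherapy delivered only: "Multivariable logistic regression analysis will be used to estimate the independent effect of malnutrition status on percent chemotherapy received", and likewise "multivariable linear regression analysis will be used to estimate the independent effect of nutritional status on mean percent chemotherapy received". The candidate covariates are "age, sex, race, ECOG status, tumor site, tumor stage, PEI, and DM", chosen by forward-stepwise selection. Apart from the Kaplan-Meier intervals, confidence intervals are tied to odds ratios and beta estimates.
- **Follow-up (Schedule of Visits).** The last contact is "Check-up 3 (end of the study, 6 months"), when OS and time to progression are recorded. The Variables section lists a date of death or loss to follow-up and a survival check at 6 months.
- **Outcomes.** OS and survival at 6 months are both listed as secondary. A general sentence says that associations between the recorded variables and the outcomes will be assessed, without naming a method.
- **Survival benchmark (Background).** Gemcitabine alone is described as having "relatively poor effect represented by a median overall survival (OS) around 6 months". Combination regimens are said to do substantially better, with no figure.

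**The concern.** Nutritional status is likely to go with stage and performance status, and both bear on survival. The plan recognises this for chemotherapy delivered, where it seeks an effect independent of ECOG and stage. For survival it names a test that cannot separate nutrition from either. The result would be a crude p-value with no adjusted hazard ratio and no interval for the size of the difference.

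The second issue is what OS means here. If each patient's observation stops at 6 months, the OS comparison and the 6-month survival comparison use nearly the same information. Presented as two outcomes, they could be read as two pieces of evidence.

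**Working it through.** **1. The plan's own figures.** The only sample-size figures are for chemotherapy delivered: 93, 163 and 356 per group for 70% vs 50%, 55% and 60%. The two-proportion formula (two-sided alpha 0.05, power 80%, pooled variance, no continuity correction) gives 92.999, 162.3 and 355.9, which round up to exactly those numbers. They serve below only as group sizes. No event count or power is stated for OS or PFS.

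**2. Confounding with no true nutrition effect.** All effect sizes and imbalances here are assumptions. At time zero, the crude hazard ratio is the ratio of the groups' mean hazards.

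*Stage alone*, with stage hazard ratio h and metastatic proportions p1 (malnourished) and p0 (well-nourished): crude HR = [1 + (h − 1)p1] / [1 + (h − 1)p0].

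| Metastatic, p0 vs p1 | h = 1.5 | h = 2.0 |
|---|---|---|
| 50% vs 70% | 1.35/1.25 = 1.08 | 1.70/1.50 = 1.13 |
| 40% vs 70% | 1.35/1.20 = 1.13 | 1.70/1.40 = 1.21 |

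*Stage and ECOG together*, taken as independent, with HR 1.6 for metastatic disease and 1.7 for ECOG 2. Well-nourished patients are 50% metastatic and 15% ECOG 2: 1.30 × 1.105 = 1.4365.

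- Malnourished 65% metastatic, 30% ECOG 2: 1.39 × 1.21 = 1.6819; ratio 1.17.
- Malnourished 70% metastatic, 40% ECOG 2: 1.42 × 1.28 = 1.8176; ratio 1.27.

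Taken over 6 months as the ratio of cumulative hazards, with overall median OS from 6 to 11 months, these become about 1.16 and 1.25 to 1.26. Imbalances of 15 to 25 points thus give roughly 1.1 to 1.25.

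*Effect on the test.* Simulation with stage imbalance only, follow-up cut at 6 months, median OS 11 months in the better stage, h from 1.5 to 2.0, 2,000 runs per scenario. Entries are log-rank rejection rates at nominal 5%.

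| Metastatic, p0 vs p1 | 93 per group | 163 per group | 356 per group |
|---|---|---|---|
| Equal (50% each) | 4–5% | 4–5% | 5–6% |
| 50% vs 70% | 6–9% | 7–12% | 10–21% |
| 40% vs 70% | 7–16% | 11–22% | 17–41% |

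The bias does not shrink as the cohort grows; the false-positive rate rises.

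**3. What a 6-month cut leaves.** With exponential survival, the proportion dead by 6 months is 1 − 2^(−6/m) for median m. At 186 patients (2 × 93):

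| Median OS, months | Dead by 6 months | Deaths of 186 |
|---|---|---|
| 6 (the gemcitabine figure) | 50% | 93 |
| 8 (assumed) | 41% | 75 |
| 9 (assumed) | 37% | 69 |
| 10 (assumed) | 34% | 63 |
| 11 (assumed) | 31% | 59 |

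**4. Overlap of OS with 6-month survival.** Simulated power for HR 1.5, 93 per group, no confounding, complete follow-up:

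| Median OS, well-nourished group | OS log-rank cut at 6 months | 6-month proportion test | OS log-rank at 18 months |
|---|---|---|---|
| 6 months | 56% | 53% | 76% |
| 11 months | 39% | 39% | 66% |

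Across all simulated scenarios, the truncated log-rank and the proportion test differed by at most about 3.5 percentage points (81% vs 77%, at 163 per group with median 6 months).

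**The case against.** **An adjusted survival model may exist elsewhere.** The article condenses a fuller protocol, it does not say log-rank is the only survival analysis, and its Outcomes section promises associations of all recorded variables with all outcomes. This stands as a limit: one cannot say that no adjusted analysis is planned. But the article gives the survival methods in some detail and names regression models for chemotherapy delivered, and none for survival. The general sentence on associations commits to no adjustment.

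**The bias is assumed.** No proportion by stage or ECOG is given, and ECOG 3 or higher is excluded. This also stands. A reader might infer that any survival difference in this study would simply be stage and ECOG. The documents do not support that: the imbalance is unknown, and a real nutrition effect is not ruled out.

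**OS is more than a proportion at 6 months.** A reader might infer that OS adds nothing. That goes too far, because death dates are recorded: Kaplan-Meier and log-rank use event timing and handle losses to follow-up. The gain in the simulation is small, but not zero. PFS has no separate 6-month counterpart, so the overlap does not concern it.

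**Low power is not an error here.** The plan claims no power for OS or PFS and promises no median OS, so few deaths by 6 months contradict nothing it states. The event counts also use the smallest of three sample-size scenarios.

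**The main hypothesis does not depend on this.** Correct: the primary outcome has multivariable logistic and linear models.

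**Conclusion.** The point holds as a limitation of two secondary outcomes. The named OS/PFS comparison is unadjusted in a non-randomised cohort, while the same section controls for ECOG and stage when the endpoint is chemotherapy delivered. A survival difference could therefore partly reflect case mix. The illustrative size, a spurious hazard ratio of roughly 1.1 to 1.25, rests on assumed imbalances of 15 to 25 points and assumed prognostic hazard ratios of 1.5 to 2.0. With balanced groups the problem would vanish.

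OS is truncated at the stated end of study and largely overlaps 6-month survival. That follows from the visit schedule; only the degree of overlap depends on the assumed exponential survival and medians. The documents do not show that confounding will occur, or that the primary result is affected.

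**What to change.** 1. Add a multivariable Cox model for OS and PFS with nutritional status and a short pre-specified set of baseline covariates: at least age, sex, ECOG and tumor stage, with others from the section's existing list as events allow. With 59 to 75 deaths, nutritional status plus four single-term covariates leaves 12 to 15 deaths per coefficient (59/5, 75/5). All eight listed covariates would leave 7 to 8 (59/9, 75/9). Stratifying by the six countries as well would be heavy for that many events.
2. Report the adjusted hazard ratio with its 95% CI as the main survival result, and keep Kaplan-Meier and log-rank as descriptive.
3. Show chemotherapy regimen only in a sensitivity analysis, because it may be chosen in response to nutritional status and so lie on the causal path.
4. Unless vital status is collected beyond 6 months, describe the outcome as overall survival truncated at 6 months, and do not present it as distinct from 6-month survival.

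The covariates are already collected, so the cost is a little more analysis work and a slightly wider interval. Extending follow-up is not required by this fix. It would change the stated end of study across centers that each hold their own ethics approval, so it costs more than a change of wording.

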#### Power Size Calculation

The expected percent of chemotherapy delivered in well-nourished patients was based on a study that assessed the chemotherapy dose intensity in gastrointestinal malignancies that included pancreaticobiliary disease during the first 8 weeks after the start of the chemotherapy (25). Based on an expected percentage of chemotherapy delivered of 70% in well-nourished patients, with a type I error of 0.05 and a type II error of 0.20, a sample size of 93 patients per group will be required in case of a percentage difference of chemotherapy delivered of 20% between well-nourished and malnourished patients, 163 patients per group in case of a difference of 15% between both groups, and 356 patients per group in case of 10% difference.

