#### Outcomes

The association between all the abovementioned variables and the following outcome variables will be assessed:

Primary outcome:

Adherence to planned chemotherapy in the first 12 weeks after the diagnosis in patients' groups stratified according to their baseline nutritional status.

Drug doses will be expressed in weight-based, body surface area (BSA)-based, AUC units or flat dose, according to standard dosing practice for a given drug or combination. For each drug in a regimen, the sum of the doses delivered during the first 12 weeks of therapy will be divided by the sum of the expected doses based on published standard schedule and dosing. The mean percent dose delivered of all drugs in a regimen will be reported as “percent of standard chemotherapy dose delivered.”

Similarly, the sum of the doses delivered during the first 12 weeks of therapy will be divided by the sum of the expected doses based on each patient's starting chemotherapy dose, and the mean percent dose delivered for all drugs in a regimen will be reported as “percent of planned chemotherapy delivered.” We will use percent of standard chemotherapy dose delivered to estimate the overall relative dose delivered, and we will use percent of planned chemotherapy dose delivered to quantify further dose reductions from starting dose and as an indicator of overall toxicity.

Secondary outcomes:

Percent of patients with chemotherapy-related toxicity in each group of patientsOS and survival at 6 monthsProgression-free survivalQuality of life that will be assessed using the European Organization for Research and Treatment of Cancer (EORTC) QLQ-PAN26 scaleNumber of hospitalizationsFactors associated with the percent of chemotherapy received.

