#### Statistical Analysis

The STROBE guidelines for observational studies will be followed to report our findings^2^. Descriptive statistics (including mean, standard deviation, median, range, frequency, and percent) will be calculated to characterize the study cohort.

Chemotherapy dosing over the first 12 weeks of therapy (i.e., percent chemotherapy received in the first 12 weeks, as defined above) will be compared between well-nourished and malnourished patients. Two-sample *t*-tests/Wilcoxon rank-sum tests will be used for MNA comparisons of mean/median percent chemotherapy received, for all patients and stratified by risk for toxicity. Two-sample *t* tests/Wilcoxon rank-sum tests and chi-square tests/Fisher's exact tests will be used, as appropriate, to compare malnutrition status between groups based on MNA, on demographic/clinical characteristics of interest.

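### The 93/163/356 per-group sizes come from a two-proportion formula, but the primary endpoint is a continuous percent dose compared by t-test or Wilcoxon; the error is conservative

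*Protocol article*

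**What the plan says.** **Sample size.** Protocol article, Power Size Calculation. The starting value is given as follows: "Based on an expected percentage of chemotherapy delivered of 70% in well-nourished patients". The error rates are stated next: "with a type I error of 0.05 and a type II error of 0.20". The article then says that "a sample size of 93 patients per group will be required in case of a percentage difference of chemotherapy delivered of 20" percent. For the two smaller differences it gives these sizes: "163 patients per group in case of a difference of 15% between both groups, and 356 patients per group in case of 10% difference". The Abstract repeats the three sizes. No SD, test or formula is named, and none of the three scenarios is chosen as the target.

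**Endpoint.** Under Outcomes, each drug's delivered dose over 12 weeks is divided by its expected dose under the published standard schedule. "The mean percent dose delivered of all drugs in a regimen will be reported as" the percent of standard dose. That is one number per patient on a continuous scale.

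**Test.** Under Statistical Analysis, two-sample t-tests or Wilcoxon rank-sum tests "will be used for MNA comparisons of mean/median percent chemotherapy received". A linear model treats the same quantity as continuous. A logistic model cuts it at 80%, but only as an adjusted analysis, and no expected rate of patients reaching 80% is given. All p "values are two-sided with statistical significance evaluated at the 0.05 alpha level".

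**Enrolment.** Study Period lets recruitment run to June 2020 or until the power calculation is met.

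**The concern.** A two-proportion formula needs a yes/no outcome and the share of patients who have it. A comparison of means needs the SD of the outcome. The sizing paragraph supplies neither a share of patients nor an SD. It supplies a dose level, 70% of chemotherapy delivered, and three differences in that level.

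If that dose level was entered into a binary formula, the three pairs of size and difference describe a different study. A reader would conclude that 93 per group can show only a 20-point effect, and that 10 points needs 712 patients (2 x 356). Because enrolment may end when the calculation is met, the figures also bear on when the study may stop.

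**Working it through.** **Inputs.** Two-sided alpha 0.05 (z = 1.9600), power 0.80 (z = 0.8416), well-nourished value 70%, differences 20, 15 and 10, equal groups. All come from Power Size Calculation and Statistical Analysis. The SD is not stated and is assumed below.

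**1. Reproducing the stated sizes.** Pooled two-proportion formula, with p̄ the mean of p1 and p2:

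n = [1.9600·√(2p̄(1−p̄)) + 0.8416·√(p1(1−p1) + p2(1−p2))]² / (p1−p2)²

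- 0.70 v 0.50: (1.9600×0.6928 + 0.8416×0.6782)² / 0.04 = 93.0, so 93
- 0.70 v 0.55: (1.9600×0.6847 + 0.8416×0.6764)² / 0.0225 = 162.3, so 163
- 0.70 v 0.60: (1.9600×0.6745 + 0.8416×0.6708)² / 0.01 = 355.9, so 356

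All three match exactly. Other variants do not match all three: unpooled 91/160/354, arcsine 93/162/356, continuity-corrected 103/176/376, one-sided 74/128/281, relative reduction 186/324/713.

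**2. Could they be two-mean sizes?** The SD that would give them is Δ·√(n/2) / 2.8016:

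- 20 points: 20×√46.5 / 2.8016 = 48.7
- 15 points: 48.3
- 10 points: 47.6

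A 0-100 variable with mean m has variance at most m(100−m). This is 2100 at 70, 2500 at 50, 2475 at 55 and 2400 at 60. The largest possible pooled SDs are therefore √((2100+2500)/2) = 48.0, √((2100+2475)/2) = 47.8 and √((2100+2400)/2) = 47.4. They are reached only if every patient receives either none or all of the standard dose. The implied SDs lie just above that ceiling.

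**3. Direction of the error.** At those maximum SDs, a t-test needs 92, 161 and 355 per group. Its power at the stated 93, 163 and 356 is 80.8%, 80.6% and 80.2%. Any smaller SD gives more power.

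**4. Size of the error over an assumed SD range.** Two-sample t-test, two-sided 0.05, equal groups, 80% power for the sizes and the detectable difference:

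| Assumed SD | n per group for 20 / 15 / 10 points | Power at 93 / 163 / 356 | Difference detectable with 93 per group |
|---|---|---|---|
| 20 | 17 / 29 / 64 | over 99.9% | 8.3 |
| 25 | 26 / 45 / 100 | over 99.9% | 10.3 |
| 30 | 37 / 64 / 143 | 99.5 / 99.4 / 99.3% | 12.4 |
| 35 | 50 / 87 / 194 | 97.2 / 97.1 / 96.8% | 14.5 |
| 40 | 64 / 113 / 253 | 92.4 / 92.2 / 91.5% | 16.5 |

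The Wilcoxon test needs about 5% more patients if the data are normal.

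**The case against.** **The error is safe.** This is the strongest reply, and it stands. The binomial variance is an upper bound for a 0-100 quantity, so the stated sizes protect the t-test whatever the SD. A reader who sees the wrong formula might infer that the study is underpowered; step 3 shows the opposite. What remains is that a size called required, and the difference attached to it, are not those of the planned test.

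**The real power is unknown.** A reader might infer that power is about 99%. That holds only for an assumed SD of 30 or less. Changes to the schedule, including stopping early, are recorded under the treatment-related variables; early stopping would spread delivered dose and could push the SD to 35 or 40, where power is about 97% or 92%.

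**Recruitment has no single target.** A reader might infer that recruitment aims at a wrong number. The article lists three scenarios, picks none and also allows a calendar end, so that is not shown. The study is also observational, and a larger sample assigns nobody to a treatment.

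**The binary analysis.** It might be argued that the sizes serve the 80% cut. The wording does not support this: 70% is described as chemotherapy delivered, not as a share of patients reaching 80%. The cited study is not at hand, so what it reported cannot be checked.

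**The source window.** The 70% was observed "during the first 8 weeks after the start of the chemotherapy", while the endpoint covers 12 weeks. A reader might count this as a second error. The article discloses it openly, and it is a planning assumption, not a mistake.

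**Condensed article.** A missing SD alone could be left to the full protocol. The finding does not rest on it; it rests on the exact match to a formula for another kind of endpoint.

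**Conclusion.** The point holds in this form: the published sizes and 80% power are those of a comparison of two proportions of patients, and the planned primary comparison is of a continuous percent dose. The article does not name its formula, but the exact match on all three figures leaves little doubt.

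The consequence is a misstated required size and detectable difference, not a shortage of patients. At assumed SDs of 25 to 40, the sizes needed for 20, 15 and 10 points are 26-64, 45-113 and 100-253 per group, against the stated 93, 163 and 356. With 93 per group, the detectable difference is about 10 to 17 points, not 20.

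This rests on equal groups, a percent dose that does not exceed 100 and the unadjusted t-test. It says nothing about the adjusted models, the log-rank comparisons or unequal nutritional groups.

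**What to change.** Replace the Power Size Calculation paragraph, and the matching sentence in the Abstract, with a two-mean or Wilcoxon calculation:

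- State the SD of percent standard dose and its source: the cited dose-intensity study if it reports one, or a pooled SD from study data computed without regard to nutritional group. Show the result over a range such as 20 to 40 points.
- Name one target difference, because Study Period ties the end of enrolment to this calculation.
- Give the required size for that difference, or the difference that 93 per group can detect.

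The cost is one rewritten paragraph and one abstract sentence. No extra patients are needed, since the stated sizes already suffice for the unadjusted t-test at any possible SD.
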